### Allocation concealment and blinding

We are unable to blind participants to their allocation as they will realise that the control condition has much less content, but both arms will have access to an online resource bank and usual care. Nonetheless, all outcome data collected use self-reported measures and direct online input by participants. The study coordinator and intervention (and control) online platform facilitator (JS) cannot be blinded to the allocation because she needs to adjust her facilitation according to the different content of the two groups.

### Data storage and security

All trial data as described above are collected through an online system linked and integrated with the intervention platform. Only the Chief Investigation (JS) and core study team members who have a role in either study facilitation or data management will have direct access to such platform and data. All data sets will be password protected. To ensure confidentiality, data dispersed to trial statisticians and wider project team members will be anonymized of any identifying participant information.

### Monitoring

#### Trial steering committee

The trial is overseen by an independent Trial Steering Committee (TSC) comprising clinical-academic experts, an independent trials statistician, and carers with experiential expertise on the subject. The TSC provides governance and guidance on the study delivery and progress. It provides a monitoring and advice function for the safety and wellbeing of the study participants. In view of the safety event data, the TSC will consider the need for appointing a separate Data Monitoring Committee (DMC) if necessary. In addition, the TSC reviewed and approved the safety protocol, usage data definitions and statistical analysis plan.

### *Safety protocol*

For this trial we have adapted the definition of adverse events commonly used in conventional clinical trials.

In addition to adverse and serious adverse events, we have devised a category labelled as “unintended consequences”. These are summarized as follows:
Unintended consequences (UCo) – incidents during which participants’ use of the intervention (or control) is interrupted and the potential distress caused is below the threshold of that described in adverse event category. Examples include participants forgetting their log-in password, platform technical issues interrupting delivering, or participants realizing their own unmet needs in light of the intervention content.Adverse events (AE) - clear evidence of distress or concerns of risk of harm towards participants or others, resulting in needs for medical and/or mental health support. However, there is no immediate or serious threat of severe harm or risk of lifeSerious adverse events (SAE) – clear evidence of immediate risk to life or welfare for the participants or others.

Monitoring of all potential safety concerns will cover both active monitoring of the online platform communications (e.g. participants’ post made on forums) and query/concerns raised by participants (e.g. those who send messages through our platform). In all circumstances, the online facilitator will contact the participant concerned and offer support through online or phone communication, in addition to signposting them to relevant local services. In the unlikely event of SAEs, we will contact the relevant local authorities (e.g. Police or social services) as appropriate. Such safety monitoring and support mechanisms are outlined in the participant information sheet.

Recording and coding of safety and untoward events will be conducted on a continuous basis. These will also be reported to the TSC prior to each of the biannual TSC meeting or at an ad hoc basis if indicated, both for consensus on coding and for safety monitoring. In the event of SAEs, these need to be reported to both the TSC chair and the sponsor within 48 hours.

Overall adverse effects, including the number of UCo, AE, and SAE, will be recorded by number of events, types and participants across both arms. In addition, we will also record and report participant withdrawals from the study.

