**Fig. 1 Fig1:**
[figure not shown]
Screenshots of COPe-support content. Detailed legend: Screenshots taken from COPe-support intervention platform

Throughout the study period, an online facilitator (JS) who is an experienced mental health nurse, monitors and moderates all the interactive functions of COPe-support. These include the forums and the inbuilt communication weblinks such as messages the participants can send through COPe-support platform asking for support or seeking information. The online facilitator also coordinates a panel of 14 expert panel members comprising psychiatrists, GPs, pharmacists, benefits advisors, CBT therapists, social worker, mental health nurse, and Expert through Experience, behind the operation of the “Ask the Experts” forum. Once a week, the facilitator also posts an update via the COPe-support announcement function to all participants with an aim to keep them engaged. In parallel to the announcement appearing on COPe-support platform, an email will automatically be generated to each of the participants. For security and confidentiality considerations, participants are required to follow a set of ground rules in using COPe-support [22]. These include the use of a self-chosen pseudonym to anonymise participation in communication and interactions online and adhering to the confidentiality principles so not to include any of their own and their cared-for individual’s person-identifiable details when making posts on either forum. We provide guidelines with examples to explain what constitute person-identifiable data and how participants can fully participate in the interactive forums without giving any such data away. If necessary, the facilitator can delete or edit posts made by participants and moderate any particular participants’ access to the forums [30].

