#### Attention-matched control: web-based information bank

To control for the attentional component of COPe-support and to account for the effects of online information provided by websites run by statutory and voluntary organisations as part of usual care, we developed a control intervention to have the identical look and “feel” as the active COPe-support intervention. We created the control condition mimicking the content of the Home page, “Resources for Carers”, and the Support section from the active intervention, also delivered through Canvas VLE (see Table 1). However, there are much less content and no interactive forums in the control nor any wellbeing promotion content. Participants can get in touch with the study team directly for support if necessary, and the control also has the same communication functionalities as the active intervention, hence participants will also be sent weekly updates. In order to encourage retention and follow-up data completion, we will offer the participants allocated to the control access to COPe-support for four months’ time, after final follow up data collection. Screenshots of the control are shown in Fig. 2.

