#### Process evaluation outcomes and data

The trial has an inbuilt process evaluation study to explore participants’ usage patterns and subjective experience of participants in using COPe-support. In order to understand when and how participants access and use the online intervention, we will collect usage data which the intervention and control platform automatically monitors and records. These include:
Number of log-ins on separate days per participant (both arms)Average page views per log-in per participant (both arms)Total time spent on the platform per participant (both arms)Average time spent per page view on the platform per participants (both arms)Total number of posts per participant made to the peer-to-peer forum (intervention arm only)Total number of posts per participant made to the Ask the Experts forum (intervention arm only)

Perceived acceptability will be determined through interviewing a purposive sample of 20% of the participants in the intervention arms of the trial after all the data collection procedures (i.e. about 36 out of the 180, or less should data saturation, that is no further data is being collected that adds to the content of existing themes, be reached in the iterative analysis process [38]). For the individual interview, purposive sampling will be used to identify participants to ensure representation of diverse experiences and views from those with ethnic minority backgrounds, different caregiving experiences and roles, and usage patterns. The interview is designed to be semi-structured and conducted over phone or Skype, suiting the participants’ preference and convenience.

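### Safety events are found partly through forum posts, which only the COPe-support arm can make, so the event counts by arm are subject to unequal detection and should not be read as comparative

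*Protocol article*

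**What the plan says.** The Safety protocol section of the protocol article names two ways in which safety events come to light. The first is active: "Monitoring of all potential safety concerns will cover both active monitoring of the online platform communications", with forum posts as the only example. The second depends on the carer: "query/concerns raised by participants (e.g. those who send messages through our platform").

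The section on the attention-matched control says that "there are much less content and no interactive forums in the control". The list of usage data under Process evaluation agrees: posts to each of the two forums are to be counted in the intervention arm only. The control section also says that "the control also has the same communication functionalities as the active intervention", and Table 1 places the Support section, with its contact link, in the control as well.

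The online facilitator "monitors and moderates all the interactive functions of COPe-support" and, according to the section on allocation concealment and blinding, is not blinded.

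On output, the Safety protocol section says that the three categories (unintended consequences, adverse events, serious adverse events) "will be recorded by number of events, types and participants across both arms". The Trial Steering Committee section adds that the committee will use the safety data when deciding whether a separate data monitoring committee is needed.

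**The concern.** A count of adverse events by arm reflects both how often events happen and how likely they are to be noticed. Here the second factor differs by arm. A COPe-support carer who writes about distress on a forum is seen by the facilitator without having asked for help. A control carer in the same state has no forum to write on, and unless other monitored communications reveal the distress, must contact the team to be noticed.

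The forums also invite the kind of disclosure that counts as an event. Table 1 lists difficult emotions among the peer forum's topics, and the safety definitions include evidence of distress and carers becoming aware of unmet needs.

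A difference in the safety table could therefore come from detection alone, and a true difference could be hidden. The committee's consensus on coding can correct how a detected event is classified, but it cannot recover events that were never detected. The article does not mention this limitation.

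**Working it through.** The plan states no figure on this point, so the check has two parts: a comparison of what each arm offers, and an illustration under stated assumptions.

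**Routes by arm**

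| Route | COPe-support | Control | Source |
|---|---|---|---|
| Monitored forum posts | yes | no | Safety protocol; control section; Process evaluation |
| Messages, Support link | yes | yes | Safety protocol; control section; Table 1 |
| Scheduled adverse-event question | none described | none described | Assessment; Data collection |

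The measures under Assessment are WEMWBS, MAKS, ECI, CWS, FQ and EQ-5D-5L. The Figure 5 legend names the same scales; the figure itself was not available for this check. Service use is collected to describe usual care, not to find events.

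**Illustration**

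Assumptions: the true risk is equal in both arms; an event has chance m of being found through messages in either arm; it has a further, independent chance f of being found through forum posts in COPe-support only. The documents give neither m nor f.

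- Control detection = m
- COPe-support detection = 1 − (1 − m)(1 − f)
- Ratio of detected events = [1 − (1 − m)(1 − f)] / m = 1 + f(1 − m)/m

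| m | f = 0.1 | f = 0.3 | f = 0.5 |
|---|---|---|---|
| 0.3 | 1.23 | 1.70 | 2.17 |
| 0.5 | 1.10 | 1.30 | 1.50 |
| 0.8 | 1.025 | 1.075 | 1.125 |

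The true risk cancels from the ratio. It is 1 only if f = 0 or m = 1.

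As counts, take 180 per arm (the intervention-arm size given under Process evaluation, with 1:1 allocation) and an assumed true risk of 10%, so 18 events per arm. With m = 0.5 and f = 0.3, control detects 18 × 0.5 = 9.0. COPe-support detects 18 × (1 − 0.5 × 0.7) = 18 × 0.65 = 11.7.

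**Direction**

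Now let forum users message less, so that the message chance in COPe-support is m′ instead of m. Detection there falls below control when 1 − (1 − m′)(1 − f) < m, that is, when m′ < (m − f)/(1 − f).

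- m = 0.5, f = 0.3: the threshold is 0.2/0.7 = 0.29. If messaging falls from 0.5 to below 0.29, COPe-support shows fewer events at equal true risk.
- m = 0.3, f = 0.3: the threshold is 0. No fall in messaging reverses the direction.

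At the first threshold the total counts balance, but a comparison limited to messages would give 0.29/0.5 = 0.57 in favour of COPe-support. A count restricted to shared routes is therefore not unbiased either.

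**The case against.** The strongest reply is that no comparative safety analysis is planned. The counts are descriptive, safety is not among the objectives or hypotheses, and the analysis section contains no safety test. This stands, and it confines the harm to interpretation of the table and to the committee's oversight.

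Second, a reader might infer that control carers can be noticed only if they message, and that their distress otherwise goes unseen. The documents do not support that. Active monitoring covers platform communications in general, with forums as an example. Both arms also complete identical wellbeing and quality-of-life scales at 10, 20 and 40 weeks, and withdrawals are recorded. These give evidence on deterioration that is symmetric between arms. They are not adverse-event questions, however, and the Safety protocol section does not use them to find events.

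Third, the article condenses a fuller safety protocol that the committee approved, and a detection-route field may already exist there. That is possible. But the asymmetry follows from the routes the article states, and an analysis plan cannot repair events that were never collected.

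Fourth, the effect will vary by category. Forgotten passwords and technical faults, two of the three examples of unintended consequences, would naturally reach the team by direct contact in both arms. This also stands: the problem bears mainly on events that involve distress or unmet needs.

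**Conclusion.** The point holds in a limited form. Forum posts are a named detection route open only to COPe-support, no described assessment asks both arms the same adverse-event question, and counts are kept across both arms. Those counts are subject to unequal detection and should not be read as comparative.

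The size cannot be derived from the documents. The range of about 1.0 to 2.2 rests on assumed m from 0.3 to 0.8 and f from 0.1 to 0.5, equal true risk, equal messaging and independent routes. A reader might infer that COPe-support counts are inflated by roughly 1.7 to 2.2 times. That band needs m = 0.3 with f of 0.3 to 0.5; at m = 0.8 the ratio is at most 1.125. Nor is the direction certain if forum posting replaces messaging.

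The primary outcome is unaffected.

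**What to change.** - Keep forum monitoring as it is.
- Record the detection route of every unintended consequence, adverse event and serious adverse event. Report counts by arm in total and by route, with a statement that detection differed by arm. Do not present the shared-route count as unbiased, because it can drop real COPe-support events that were disclosed only on a forum.
- For assessments still to come, add one identical self-report item on distress needing medical or mental health support to the existing 10-, 20- and 40-week online questionnaires in both arms. Base any between-arm safety statement on that item.
- Give the Trial Steering Committee the counts by route as well as in total.

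The route code is one field in the event log and may be recoverable for past events. The new item needs a minor amendment and under a minute of each participant's time. It cannot cover assessments already completed, so earlier cohorts will have incomplete data, and it will bring in more reported events to review.

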### Trial status and review

The trial is registered with the Current Controlled Trials registration under the title “Randomised controlled trial of COPe-support online resource for carers” (ISRCTN 89563420 [10.1186/ISRCTN89563420], registration date: 02/03/2018). This study has also been reviewed and approved by South Central – Oxford C Research Ethics Committee (Reference: 18/SC/0104) and Health Research Authority (Reference: IRAS 240005). Recruitment for the trial commenced in March 2018 and will continue till early 2020. Participants are covered by indemnity and insurance for harm associated with the protocol provided by the Sponsor, St George’s, University of London.

### Data analysis

#### Statistical analysis plan

The data analysis will be performed by the trial statisticians who will be blind to randomized allocation for the primary and secondary outcome analysis. Primary analyses will be undertaken on an intent-to treat (ITT) basis, including all participants who were randomized and supplied at least one post-randomisation measure at 10, 20, or 40 weeks, regardless of usage status or withdrawal from the study. For the primary analysis, a linear mixed model will be used. The model will include participant and cohort as random effects and arm, time (10, 20, 40 weeks), the randomization stratification variable gender as well as baseline score and a time-by-arm interaction. In order to improve precision we will adjust for variables parent (Y/N) and living with the cared-for individual (Y/N). The model’s assumptions for random effects distributions and residuals will be investigated. If assumptions are not appropriate then transformation will be considered. This model will be used to estimate the mean difference and 95% CI in WEMWBS between arms at the 20-week time point (i.e. primary endpoint) though we will also explore and report the intervention effect at week 10 and 40. The model will be fitted using restricted maximum likelihood (REML). Secondary outcome measures will be assessed using similar approach. No interim analyses will be performed.

It is unlikely that missing baseline data will be problematic for the analysis as baseline outcomes are required to be collected prior to randomization. Further, as the analysis uses a mixed model which is efficient for missing data under the missing at random assumption [41] no multiple imputation will be performed. Sensitivity analysis will include exploring the mean WEMWBS score at each time point if all participants with missing information was set at the highest and lowest values seen in the dataset.

Further analysis after the analyses of primary and secondary outcomes will not be blind as this is not feasible. The intervention effect in those that use COPe-support (defined as having at least two logins) will be estimated using a complier adjusted case analysis (CACE) with “usage” treated as both a binary and ordinal variable.

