### Sample size

The trial sample size is calculated with reference to an earlier study testing a digital health intervention targeting siblings of individuals with first episode psychosis [39] and the primary outcome measure data (i.e. WEMWBS [29]). This study is powered to detect the minimum clinically important difference of + 3 in WEMWBS which is considered a meaningful change post intervention between treatment groups [31]. Using 80% power, significance level of 5% and an estimated SD of 9 from the E Sibling Project RCT baseline results [13, 39], 143 carers per arm are needed. With estimated 20% attrition, additional participants (*n* = 74), will be recruited, leading to an overall sample size of 360 across both arms.

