While optimising all the potentials the internet offers into the study and intervention design, we are aware of the challenges common amongst digital interventions and online trials. Because digital interventions allow their users a self-directed approach in using the content, intervention usage or adherence is often much more heterogenous [23, 47]. Trial attrition and disengagement are also expected issues [23, 25]. To account for potential drop out and disengagement, we have devised a facilitation protocol alongside the delivery of COPe-support, drawing strategies and ideas through extensive consultations with carers and a usability study on the intervention-prototype [22, 30]. We have used conservative recruitment and retention estimation taking lessons from the few other similar trials with carer populations [39, 48]. Furthermore, we have also used a trial design that includes an internal pilot with keen monitoring on these parameters. We will review and revise our strategies at end of pilot to scale up to the full trial accordingly. In terms of the usage issue, we have put in place several strategies. We recognise COPe-support is a novel intervention delivered through the internet, and as such a conventional “adherence threshold” or per protocol usage pattern would not be appropriate. As no literature-based usage was identified [6], we consulted experts through experience and clinical and academic experts in the field to identify and define the meaningful usage definitions used in the study protocol. We are particularly interested in understanding (1) how carers will use COPe-support, and (2) if there is a differential intervention effects in those who have decided to log-in COPe-support twice or more and use it in different extent. For such goals, we consider it important to carry out the “complier average causal effect” (CACE) analysis [23, 27]. This is because the primary analysis using the ITT model, although the gold standard, will have neglected the usage effects, if any.

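### The one missing-data sensitivity analysis named in the article does not target the 20-week arm difference and, read plainly, does not let the missing-data assumption differ by arm

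*Protocol article*

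**What the plan says.** All of this is in the Protocol article. Under Statistical analysis plan, the primary mixed model is used to "estimate the mean difference and 95% CI in WEMWBS between arms at the 20-week time point". The analysis set is described as intention-to-treat, "including all participants who were randomized and supplied at least one post-randomisation measure at 10, 20, or 40 weeks". Because the model is considered efficient under missing at random, "no multiple imputation will be performed". The sensitivity analysis for missing data is introduced as including one item: "exploring the mean WEMWBS score at each time point if all participants with missing information was set at the highest and lowest values" found in the dataset.

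The text does not say that the arm difference will be re-estimated, whether the means are taken by arm, or that the imputed value may differ between arms.

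The Sample size section allows for 20% attrition, and the Discussion says: "Trial attrition and disengagement are also expected issues".

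**The concern.** A sensitivity analysis for missing data should show how far the missing-at-random assumption can fail before the main conclusion changes. Here the conclusion is the arm difference at 20 weeks. The departure that could bias it is dropout related to wellbeing in a way that differs between arms.

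The design makes that foreseeable. Participants are not blinded and will notice that the control has much less content (Allocation concealment and blinding). Only control participants are promised later access to COPe-support as an encouragement to stay (Attention-matched control). The outcome is self-reported.

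The named check is aimed at a different quantity, the mean score. If a difference is derived from it, one extreme value has been given to everyone missing. A reassuring result would then be weak evidence of robustness, and an alarming one might reflect only unequal dropout numbers.

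**Working it through.** **Inputs from the article.** Target difference 3 and SD 9 ("minimum clinically important difference of + 3 in WEMWBS"; "Using 80% power, significance level of 5% and an estimated SD of 9"); "143 carers per arm are needed"; 20% attrition; 360 in total, so 180 per arm at 1:1. The possible WEMWBS range is 14 to 70, the outer limit for any observed extreme.

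**Assumptions.** Two-sided test, in line with the planned 95% CI. Observed means 46 (intervention) and 43 (control), a difference of 3. Observed extremes 14/70, with 20/68 and 25/65 as narrower alternatives. No baseline adjustment in the standard errors.

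**Plan's own figure.** n per arm = 2 x 81 x (1.96 + 0.84)^2 / 9, which gives 142; the t-based calculation gives 142.2, rounded up to 143. Then 286 / 0.8 = 358, and 286 + 74 = 360. The sample size reproduces.

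**Step 1: the check as a formula.** With fractions pI and pC missing and one value v for all missing participants:

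difference = (1 - pI) x 46 - (1 - pC) x 43 + (pI - pC) x v

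**Step 2: equal attrition, 20% in each arm.** The term in v vanishes. The difference is 0.8 x 3 = 2.4 for the highest value, the lowest value or any other. The two scenarios therefore give one answer, which amounts to assuming no arm difference at all among those missing.

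**Step 3: unequal attrition, 25% intervention v 15% control.** The difference is 34.5 - 36.55 + 0.10 x v.

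| Extremes (low/high) | All lowest | All highest | Swing |
|---|---|---|---|
| 14/70 | -0.65 | 4.95 | 5.6 |
| 20/68 | -0.05 | 4.75 | 4.8 |
| 25/65 | 0.45 | 4.45 | 4.0 |

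The swing is the attrition gap (0.10) times the range of the extremes. It is larger than the 3-point target in every row, with no assumption made about how dropouts in either arm actually fared.

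**Step 4: precision under equal 20% attrition.** Variance in an arm = 0.8 x 81 + 0.16 x (v - arm mean)^2; SE = sqrt(sum of the two variances / 180); z = 2.4 / SE. For v = 14: sqrt((228.64 + 199.36) / 180) = 1.54, z = 1.56. For v = 70: sqrt((156.96 + 181.44) / 180) = 1.37, z = 1.75. For v = 25 and v = 65, SE is 1.18 and 1.21, z = 2.03 and 1.98. With observed data only, SE = 9 x sqrt(2/143) = 1.064 and z = 2.82. Whether significance is lost therefore depends on the most extreme scores in the dataset.

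**Step 5: the question that matters.** If the 20% missing in the intervention arm score delta points away from their missing-at-random expectation, the difference is 3 + 0.2 x delta.

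- delta -3, -5, -9, -15 gives 2.4, 2.0, 1.2, 0.0.
- The same shift in both arms leaves it at 3.0.
- Taking the SE as about 1.064, significance needs a difference of 1.96 x 1.064 = 2.09, so the tipping delta is about (2.09 - 3) / 0.2 = -4.6 points.

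A reader can judge whether -4.6 points is plausible. The named check does not yield such a figure.

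**Step 6: the alternative reading, opposite extremes by arm.** At 20% missing, difference = 2.4 ± 0.2 x (high - low): -8.8 to +13.6 for 14/70, and -5.6 to +10.4 for 25/65. Bounds this wide would overturn almost any result.

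**The case against.** The strongest reply is that this is one condensed sentence in a journal article. Sensitivity analysis is said to include the check, which is not an exhaustive list. A full analysis plan is available on request (Mediation measures analysis) and was approved by the steering committee. A reader might infer that no other missing-data analysis is planned. The article does not support that, and the absence of further checks is not part of this point. The point concerns the method that is stated.

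Other stronger readings also go too far:

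- **That the check can never reveal a problem.** Exact cancellation needs equal attrition. With a 10-point gap the check can remove or reverse the difference (step 3), although for a mechanical reason.
- **That a trial hitting its 3-point target would lose significance under this check.** This holds for extremes of 14/70 and 20/68 (z 1.79 and 1.84 for the latter), but not for 25/65. The article uses the observed extremes, not the scale limits, and states no test for this check.
- **That the primary analysis is unsound or its set mislabelled.** The set is openly defined. Under missing at random, a participant with a baseline score but no follow-up adds nothing to this likelihood model. Such participants matter only when departures from that assumption are examined.

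It is also fair that taking means by arm and using the same value in both arms are readings of the sentence. If means are reported by arm, a difference follows by subtraction, and steps 2 and 3 then apply. Reminders, vouchers, weekly updates in both arms and a pilot that met its 80% retention criterion reduce the risk of differential dropout without removing it.

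**Conclusion.** The concern stands in limited form. The named check is not directed at the primary estimate and, on its plain reading, does not let the missing-data assumption differ by arm. Under equal 20% attrition it only shrinks the difference from 3.0 to 2.4. Under 25% v 15% it moves the difference by 4.0 to 5.6 points through the attrition gap alone. Either way it says little about plausible arm-specific departures from missing at random.

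The equal-attrition result needs no assumption about means or extremes. The unequal-attrition and z figures rest on assumed means, extremes and dropout rates, and the z values are unadjusted for baseline. The primary model remains valid under missing at random. This is a moderate, inexpensive improvement to the robustness analysis and does not bar the trial from proceeding.

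**What to change.** Replace or supplement the highest/lowest check, unless the full analysis plan already does so, with a delta-adjusted (pattern-mixture) re-estimate of the 20-week arm difference:

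1. Include all randomised participants, also those with no follow-up score.
2. Impute under missing at random within arm.
3. Shift the imputed scores by a pre-specified range of deltas in the intervention arm only, the control arm only, and both. A range of 0 to -6 (twice the 3-point target) is one example.
4. Report the difference and 95% CI at each delta, and the delta at which the conclusion changes.
5. Word the exclusion of multiple imputation so that it applies to the primary model only.

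Coded arm labels keep the statisticians blind. Log-in data exist for both arms and could serve as auxiliary variables, but this is optional: the control has far less content, so usage may hint at allocation, and these data are collected only after 40 weeks.

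The cost is a small amount of programming and a choice of delta range, to be fixed before unblinding. No new data are needed and the primary model does not change.
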